##### Work and activity

The Work Productivity and Activity Impairment (WPAI) [53], 6-item questionnaire is a well validated instrument to measure impairments due to overall health and symptoms in work and activities.

### Participant timeline

After a telephone screening, the patients corresponding to the eligibility criteria are invited to participate in the study with a first appointment for the baseline. The full assessment protocol is then administered. Individuals completing the inclusion criteria are randomized within one week of baseline and intervention can start the following week. The intervention sessions are proposed with a week interval followed by a reactivation session 1 month after the 4th session. Immediate and long-term follow-up will be administered 2 and 8 months after the end of intervention. This timeline is summarized in Fig. 1.

**Fig. 1 Fig1:**
[figure not shown]
Participant timeline

### Sample size

The uniqueness of our research does not make it possible to determine the exact expected effect size. Thus, we decided to follow a proof-of-concept study logic with a pragmatic approach to setting our sample size. A feasibility analysis led us to the conclusion that we could reach a sample of 130 participants in 10 months. We next measured the sensitivity of our experimental design on this expected recruitment rate with Gpower [54] based on the following values: alpha corrected for 2 primary outcomes equal to 0.025, power equal to 0.80, experimental design corresponding to a mixed analysis of variance with repeated measures and an intergroup variable, with an intra-subject correlation of 0.5. Results from the sensitivity analysis show that our experimental design will be able to detect small effect sizes (interaction effect in a mixed anova) of f = 0.137.

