### Trial design

COVCOG is a multicenter, randomized controlled proof-of-concept trial conducted with two parallel groups (ratio 1:1) comparing psychoeducation interventions that focus on cognitive (*n* = 65) versus affective (*n* = 65) difficulties. Randomization with minimization will be used.

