#### Primary outcome analysis

Primary outcome will be first analyzed on an intention-to-treat (ITT) basis, including all patients as originally allocated after randomisation. For missing information due to patient drop-out, we will rely on the linear mixed model and consider the baseline data as part of the outcome matrix. We will also perform a per-protocol (PP) sensitivity analysis including only those patients who completed the treatment originally allocated.

Analyses should be considered as hypotheses generating. To explore the effects of the intervention type on the two primary outcome measures, the results will be compared using linear mixed models. More precisely, the moment of the measure (baseline and immediate follow-up), the intervention (nested within the centers), the centers and the interaction of these factors will be considered as fixed factors. A nested random intercepts and slopes for each participant within the centers will be implemented. Age groups, educational level, objective Z-score (Z-score from 0 to -0.50; -0.51 to -1, etc.) and gender will also be included in the model as stratification factors. Following the linear mixed model, linear contrast will be performed between the two levels of the intervention variable on the first follow-up measure (T1) to explicitly compare the potential benefit of the intervention. Bonferroni adjustment will be performed to correct for multiple testing, more precisely 2 tests (the number of primary measures), and p-value < 0.025 will be considered as statistically significant. 95% CI and standardized effect sizes (SES) from the null model will be calculated. The following convention will be used to interpret effect size: small 0.2–0.49, moderate 0.5–0.79, large ≥ 0.8. As a Proof-of-Concept (POC) study, estimation will be focused on ES but will include p-values as help in interpreting the data.

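### The detectable effect f = 0.137 is computed correctly, but under that calculation it is a between-arm difference of about 0.55 SD, which the protocol's own scale calls moderate, not small

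*Protocol article*

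**What the plan says.** The Sample size section explains that the number of patients came from feasibility ("we could reach a sample of 130 participants in 10 months") and that the sensitivity of the design was then worked out for that number. The settings were "alpha corrected for 2 primary outcomes equal to 0.025, power equal to 0.80", an "experimental design corresponding to a mixed analysis of variance with repeated measures and an intergroup variable", and the assumption "with an intra-subject correlation of 0.5". The conclusion drawn is that "our experimental design will be able to detect small effect sizes (interaction effect in a mixed anova) of f = 0.137". The Trial design section gives equal arms: "focus on cognitive (*n* = 65) versus affective (*n* = 65) difficulties".

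The Primary outcome analysis section describes a linear mixed model with two occasions, "the moment of the measure (baseline and immediate follow-up", followed by a contrast between the two arms at the first follow-up (T1). It then fixes how effects will be read: "The following convention will be used to interpret effect size: small 0.2–0.49, moderate 0.5–0.79, large ≥ 0.8". The protocol does not convert f = 0.137 to that second scale.

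**The concern.** The protocol uses the word small on two scales. In the sample size statement it describes Cohen's f for a group-by-time interaction. In the analysis section it describes a standardized effect size with numerical bands. A reader who takes the bands from the analysis section back to the sample size section will conclude that the trial is powered for between-arm differences somewhere in 0.2–0.49. If f = 0.137 corresponds to a larger difference, that conclusion is wrong.

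What is at stake is the reading of the result, especially a non-significant one. Both arms are active interventions, and the Discussion advises caution about the predicted superiority of the cognitive arm, so a modest true difference is plausible.

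**Working it through.** **Inputs.** N = 130, alpha 0.025, power 0.80, correlation rho = 0.5 and the mixed ANOVA interaction come from Sample size. The 65 per arm come from Trial design. The two time points, the T1 contrast and the bands come from Primary outcome analysis.

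**Step 1: reproduce the stated figure.** For a within-between interaction with k = 2 groups and m = 2 time points, G*Power's default form is

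- lambda = f² × N × m / (1 − rho), with df1 = (k − 1)(m − 1) = 1 and df2 = (N − k)(m − 1) = 128.

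Solving the noncentral F test for 80% power at alpha 0.025 gives f = 0.1365. At f = 0.137 power is 80.3%. The stated value is therefore right, and it belongs to two time points: three would give 0.122.

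**Step 2: convert f to a difference.** Let the arms be equal at baseline, as randomization implies in expectation, and differ by d SD at follow-up. In the 2 × 2 table of means each interaction effect is ± d/4. Hence f = d/4 and d = 4f:

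- 4 × 0.1365 = 0.546 SD; with the rounded figure, 4 × 0.137 = 0.548 SD.

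**Step 3: cross-check.** At rho = 0.5 the SD of the change score is sqrt(2 × (1 − 0.5)) = 1 raw SD. The difference in change and the unadjusted T1 difference therefore have the same standard error, sqrt(2/65) = 0.175 SD. A two-sided t test at 0.025 with 128 df reaches 80% power at 0.546 SD. A simulation of 40,000 trials with a true difference of 0.548 SD gave 80.4% power for both the change score and the T1 contrast.

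**Step 4: power inside the small band** (65 per arm, noncentral t with noncentrality d/0.175):

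| True difference (SD) | Power, calculation as stated | Power, full baseline adjustment |
|---|---|---|
| 0.20 | 13% | 17% |
| 0.30 | 29% | 39% |
| 0.40 | 51% | 64% |
| 0.49 | 70% | 83% |
| 0.548 | 80% | 91% |

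By the normal approximation, 80% power would need 476 per arm at 0.20 SD, 156 at 0.35 and 80 at 0.49.

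**Step 5: how far 0.55 SD depends on the model.**

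- *Baseline adjustment.* The residual SD at rho = 0.5 is sqrt(1 − 0.25) = 0.866, so the detectable difference is 0.546 × 0.866 = 0.473 SD.
- *Higher correlation (assumption).* For the difference in change, rho = 0.6 gives 0.49 SD and rho = 0.7 gives 0.42 SD. An unadjusted T1 contrast stays at 0.546 SD.
- *Loss to follow-up (assumption; the document gives no rate).* With 15% loss, about 55 per arm, the figure is 0.595 SD. With 20% loss, 52 per arm, it is 0.612 SD. The baseline-adjusted figures are then about 0.52 and 0.53 SD.

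**The case against.** The strongest reply is that nothing has been miscalculated. The sample size sentence names its metric beside the label, small belongs to the f scale, and the bands in the analysis section are set for a different statistic. This stands as far as the number goes: a reader might infer that f = 0.137 is an arithmetic error, and it is not. It does not rescue the label, because the protocol interprets its results on the other scale and offers no conversion.

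Second, 0.55 SD lies close to the cut-off and depends on the model. The mixed model takes baseline into the outcome matrix and includes several stratification factors, so the real analysis may be more precise. This stands in part. The protocol states no constraint of equal arms at baseline, the sample size calculation claims no such gain, and full adjustment moves the figure only to 0.47 SD, the top edge of the small band. The denominator of the standardized effect size is also not spelled out; the conversion above uses the total SD at a single time point, as f does.

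Third, a reader might infer that the trial cannot detect small effects, or has little power anywhere in the small band. The figures do not support that: power is 51% at 0.40 SD and 70% at 0.49 SD. What holds is that it does not reach 80% anywhere in the band.

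Fourth, a reader might infer that the investigators intend to treat a null result as excluding a small benefit. The document does not say so. It calls the analyses hypothesis generating, puts estimation first, reports confidence intervals and uses p-values as an aid. The sensitivity statement also did not set the sample size. This lowers the consequence but does not make the label right.

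**Conclusion.** The point holds as a mislabelled sensitivity statement. With 130 patients analysed, two time points, correlation 0.5, alpha 0.025, 80% power and no baseline adjustment, the detectable between-arm difference is about 0.55 SD. On the protocol's own scale that is moderate. Describing it as small is wrong on the scale used to interpret results, because under that calculation 80% power is not reached at any value from 0.2 to 0.49.

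The conversion rests on the total SD at one time point as denominator. If the T1 contrast were fully baseline-adjusted, the upper edge of the small band, from about 0.47 SD, would come within reach with all 130 analysed; power at 0.20 SD would still be only 17%. The loss figures are illustrations and carry no weight in the rating. Severity is moderate: neither the design nor the analysis is affected, only what the trial is said to be able to show.

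**What to change.** Replace the closing sentence of the Sample size section with wording such as:

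> With 130 patients analysed, alpha 0.025, 80% power and correlation 0.5, the detectable between-arm difference is about 0.55 SD (f = 0.137), which is moderate on our scale. The trial does not have 80% power for small differences, and a non-significant result does not exclude them.

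Add two qualifiers: the figure rises to about 0.6 SD if 15–20% of patients lack T1 data (an assumption, to be replaced by the team's own expectation), and it would be about 0.47 SD only if the T1 contrast is baseline-adjusted. If adjustment is intended, the analysis section should say so, so that the figure quoted matches the model.

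The cost is a few lines of text and a less favourable stated sensitivity. No extra patients are needed and the planned analysis need not change. If the article can no longer be altered, the same statement can go into the analysis plan or the report of results.

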### Recruitment

An initial set of patients will be identified by the usual physicians/clinical teams of the centers participating in the study. Patients will be informed and will contact the study team. Participants will also be recruited by word of mouth ("flyer", Covid long facebook group, primary care physicians). Finally, if needed, patients who had a post-Covid follow-up consultation in one of the centers will be contacted again.

### Assignment of interventions: allocation

#### Sequence generation

Given our small sample size, and because individuals with more severe cognitive impairments might respond differently to the intervention than those with milder difficulties, we will use randomization by minimization. Although severity and interval since COVID episode are probably important prognostic factors in outcomes, we decided to achieve trial arm balance only on age, education level, gender, Centre, and severity of cognitive deficits and complaints. For cognitive deficits, scores will first be Z-scored based on normative data, and next a global Z-score calculated on all variables will be considered (sum of Z-scores divided by number of measures). A Z-score will also be calculated for both tools assessing cognitive complaints. For both these objective and subjective indices, balance will be done by Z-score range of 0.5 (e.g., Z-score from 0 to -0.50; -0.51 to -1, etc.). For age we will use 18–29; 30–39; 40–49; 50–59; 60–70. For education, we will use 4 levels: 1. primary or professional education; 2. secondary education; 3. bachelor; 4. master. In the calculation of the imbalance each arm and each prognostic factor will have the same weight. The imbalance score is calculated based on all previous allocations as well as the current participant's hypothetical allocation to each treatment. The distance measure used to calculate the imbalance score is the marginal balance. If there is no imbalance, the allocation will be completely random. If there is an imbalance, the treatment with the lowest imbalance score is chosen with a 75% probability.

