#### Secondary outcome analysis

Mixed linear models will also be used to assess the maintenance of effect across time (baseline, immediate and long-term follow-up). We will re-run the same analysis as for primary outcome, this time by including scores at long-term follow-up. Intervention effect size will be estimated using the same mixed models for each secondary and exploratory outcome measurement (Scores of ISQV and EQ-5D, the 5 overall Z-score per cognitive domain, Outcome-Questionnaire 45, PSQI, M-FIS) at both short-term follow-up (T1) and long-term follow-up (T2). As a rule, stratification factors will be included in the analyses.

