### Interim analyses

The objective of interim analyses will be to determine if there exist profiles of patients with specific characteristics, to assess if the interventions act differently according to subgroup. We hypothesize a subdivision of patients according to the presence of a more cognitive or psychological profile. For this Latent Profile Analysis (LPA), the z-standardized mean scale scores of the following variables will be entered in the model: composite scores for memory, attention and executive performance, global score at OCQ and M-FIS. All this continuous variables will be used If the presence of these two sub-groups is confirmed, we will next assess if they differ on primary outcomes (complaints at BRIEF and MMQ scales), quality of life (ISQV), medical variables (length of potential hospitalization; presence and duration of ventilation; presence of neurological symptoms at acute phase time since infection), presence/absence of antecedent psychological difficulties, age and sex.

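### Two factors the protocol itself expects to be prognostic, acute COVID severity and time since infection, are neither minimised nor named in any outcome model whose covariates are listed, although the data are recorded

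*Protocol article*

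**What the plan says.** All references are to the protocol article.

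- **Allocation (Sequence generation).** "Although severity and interval since COVID episode are probably important prognostic factors in outcomes, we decided to achieve trial arm balance only on" the following: "age, education level, gender, Centre, and severity of cognitive deficits and complaints". Since severity of deficits and complaints is in the balanced list, the severity left out is read here as that of the COVID episode.
- **Primary model (Primary outcome analysis).** Besides the time of measurement, "the intervention (nested within the centers), the centers and the interaction of these factors will be considered as fixed factors". For covariates: "Age groups, educational level, objective Z-score (Z-score from 0 to -0.50; -0.51 to -1, etc.) and gender will also be included in the model"; these are treated as stratification factors. Baseline data are treated as part of the outcome, and the arms are contrasted at two months (T1).
- **Later models.** For the eight-month data: "We will re-run the same analysis as for primary outcome, this time by including scores at long-term follow-up". Secondary outcomes use the same models, with the stratification factors as the general rule. The subgroup model (Methods for additional analyses) adds only the latent-profile group.
- **Data recorded (Interim analyses).** The medical variables used to compare the latent profiles are "length of potential hospitalization; presence and duration of ventilation; presence of neurological symptoms at acute phase time since infection".

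**The concern.** The plan names two likely predictors of outcome, leaves their balance to chance, and then does not adjust for them.

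The document gives some reason to expect that they matter. Entry opens three months after infection with no stated upper limit (Eligibility criteria), and randomisation runs from April 2022 to August 2023 (Trial status), so intervals may vary widely. Background and rationale describes gradual improvement after one year and beyond 16 months, and links memory deficits to respiratory distress in the acute phase.

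At stake is the precision of an effect estimate from 65 patients per arm, and the freedom to adjust afterwards. Baseline significance tests on clinical characteristics are planned (Summary of baseline data and flow of patients). If one of them flags either factor, any adjustment would be a post hoc choice.

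**Working it through.** **1. The plan's own figure.** Inputs from Sample size: N = 130, alpha 0.025, power 0.80, within-subject correlation 0.5, two arms; two time points taken from the primary model. For the within-between interaction, λ = f² × N × m / (1 − ρ) = 0.137² × 130 × 2 / 0.5 = 9.76, on 1 and 128 degrees of freedom. Power is 0.803, and 80% power is reached at f = 0.1365. The stated 0.137 reproduces.

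**2. Which factors are covered.**

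| Factor | Minimised | In the listed models |
|---|---|---|
| Age, education, gender, centre | yes | yes (age in bands) |
| Objective deficit Z-score | yes | yes (in bands) |
| Complaint scores | yes | as the outcome, baseline included |
| Acute COVID severity | no | no |
| Time since infection | no | no |

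**3. Chance imbalance with 65 per arm.** For a standardised covariate that is not balanced and is unrelated to the balanced ones:
- SD of the arm difference = √(2/65) = 0.175
- 95% limits = ±1.96 × 0.175 = ±0.34 SD
- mean absolute difference = 0.175 × √(2/π) = 0.14 SD

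For a binary severity marker the limits are ±1.96 × √(2p(1 − p)/65). That is about ±14 percentage points at p = 0.20 and ±17 points at p = 0.50. Both prevalences are assumptions.

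**4. Shift in the T1 contrast.** The documents give no prognostic strength. Assume a correlation r of 0.2 to 0.3 with the T1 score.
- At the edge of the 95% range: 0.344 × 0.2 = 0.07 SD to 0.344 × 0.3 = 0.10 SD
- On average: 0.14 × 0.2 = 0.03 SD to 0.14 × 0.3 = 0.04 SD

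**5. Gain in precision.** The standard error is multiplied by √(1 − r²):
- r = 0.2: √0.96 = 0.980, a 2.0% reduction
- r = 0.3: √0.91 = 0.954, a 4.6% reduction

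**6. The same gain as power.** If the two factors explain a share R² of residual variance (assumption):

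| R² | Detectable f | Power at f = 0.137 |
|---|---|---|
| 0 | 0.1365 | 0.803 |
| 0.05 | 0.133 | 0.824 |
| 0.10 | 0.130 | 0.846 |

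**7. Cost in parameters.** Two single-parameter covariates, each with a main effect and a time interaction over two time points, add 2 × 2 = 4 fixed-effect parameters.

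**The case against.** The choice is disclosed, and leaving a covariate out of a randomised linear comparison causes no bias. That stands.

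A reader might infer that nothing in the trial protects against these factors. The documents do not support this. Whatever part of their effect is already visible at baseline is partly balanced by minimising on deficits and complaints, and partly modelled because baseline is in the outcome matrix. Only the residual effect on later change is uncovered. The r that matters is therefore the one left after these terms, and it may be below 0.2 to 0.3.

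A reader might also set the 0.07 to 0.10 SD shift against the 0.2 at which the plan's small effects begin. That shift is the edge of the 95% range; the average is 0.03 to 0.04 SD. It is also already contained in the standard error of the contrast and is not a further error on top of it.

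Nor are the factors excluded from every analysis. The exploratory growth-curve models list no predictors, so there they are simply unspecified.

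Background and rationale also reports similar incidence of fatigue and cognitive impairment in hospitalised and non-hospitalised patients, before and after six months. The slow recovery it describes concerns test performance, while the primary outcome is complaints. This weakens a hospitalised-or-not marker. It concerns prevalence, however, and not change after an intervention, so it does not overturn the protocol's own statement that the two factors are likely to be prognostic.

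Lastly, an analysis plan not shown here may add covariates. The list written in this document nevertheless omits them, and the document gives no reason.

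**Conclusion.** The point holds as a modest matter of efficiency and prespecification. The protocol expects two factors to be prognostic, records time since infection and markers of acute severity, and uses neither in minimisation or in any outcome model whose covariates it lists.

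The treatment comparison remains unbiased. The loss is roughly 2 to 5% in standard error if r is 0.2 to 0.3, together with exposure to chance imbalance within about ±0.34 SD of the covariate. These sizes rest on the assumed r, on 65 analysed per arm, and on covariates unrelated to the minimised factors; any such relation narrows the imbalance limits. The change is still worth making because the baseline data are already in hand.

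**What to change.** Prespecify two baseline covariates in the primary and secondary models:

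- time since infection, continuous, for example on the log scale;
- one defined acute-severity variable derived from what is already recorded (hospitalisation, ventilation, acute neurological symptoms), with its definition fixed before the arms are compared.

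Give each a time interaction so that it can act on T1 and not only on the overall level.

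The cost is analysis wording and about four fixed-effect parameters in the primary model, which is small for 130 patients. With three time points treated as categories, the long-term model would need 2 × 3 = 6. No new data are required.

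Optionally, enter age and the objective Z-score as continuous terms. The bands mirror the minimisation categories and are not an error, but they discard information that is available.
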